## Abstract

**Background:**

The cardiovascular risk in renal transplant patients is increased in patients who continue to smoke after transplantation.

The aim of the study is to measure the effectiveness of exhaled carbon monoxide (CO) measurement plus brief advisory sessions, in comparison to brief advice, to reduce smoking exposure and smoking behavior in kidney transplant recipients who smoke. The effectiveness will be measured by: (1) abandonment of smoking, (2) increase in motivation to stop smoking, and (3) reduction in the number of cigarettes smoked per day.

**Methods/design:**

Design: a randomized, controlled, open clinical trial with blinded evaluation.

Scope: A Coruña Hospital (Spain), reference to renal transplantation in the period 2012–2015.

Inclusion criteria: renal transplant patients who smoke in the precontemplation, contemplation or preparation stages according to the Prochaska and DiClemente’s Stages of Change model, and who give their consent to participate.

Exclusion criteria: smokers attempting to stop smoking, patients with terminal illness or mental disability that prevents them from participating.

Randomization: patients will be randomized to the control group (brief advisory session) or the intervention group (brief advisory session plus measuring exhaled CO). The sample target size is *n* = 112, with 56 patients in each group. Allowing for up to 10 % loss to follow-up, this would provide 80 % power to detect a 13 % difference in attempting to give up smoking outcomes at a two-tailed significance level of 5 %. Measurements: sociodemographic characteristics, cardiovascular risk factors, treatment, rejection episodes, infections, self-reported smoking habit, drug use, level of dependence (the Fagerström test), stage of change (Prochaska and DiClemente’s Stages of Change model), and motivation to giving up smoking (the Richmond test).

Response: the effectiveness will be evaluated every 3, 6, 9 and 12 months as: pattern of tobacco use (self-reported tobacco use), smoking cessation rates, carbon monoxide (CO) levels in exhaled air measured by CO-oximetry, urinary cotinine tests, nicotine dependence (Fagerström test), motivational stages of change (Prochaska and DiClemente’s stages) and motivation to stop smoking (the Richmond test).

Analysis: descriptive statistics and linear/logistic multiple regression models will be performed. Clinical relevance will be measured as relative risk reduction, absolute risk reduction and the number needed to treat.

Ethics: informed consent of the patients and Ethical Review Board was obtained (code 2011/061).

**Discussion:**

Tobacco is a modifiable risk factor that increase the risk of morbidity and mortality in kidney transplant recipients. If effectiveness of CO-oximetry is confirmed to reduce tobacco exposure, we would have an intervention that is easy to use, low cost and with great implications about cardiovascular risk prevention in these patients.

**Trial registration:**

Current Controlled Trials ISRCTN16615772.

EudraCT number: 2015-002009-12.

## Background

Cigarette smoking is a well-established risk factor for cardiovascular disease and cancer [1]. An adverse effect of smoking on renal function has also been described. Although the exact mechanisms of smoking-induced renal damage remain to be determined, there is clinical evidence that smoking has important adverse effects on renal outcome in various kidney diseases, such as diabetic nephropathy, hypertensive kidney disease, and primary glomerular diseases, as well as for patients who require hemodialysis chronically [2–4]. In renal transplant recipients, who already have a higher risk of cancer [5, 6] and cardiovascular disease [7] than the general population, smoking should probably be viewed as an even more risky behavior.

Despite its well-known harmful effects, smoking prevalence is still high, predominantly in developing countries. The latest World Health Organization (WHO) population survey demonstrated a 29 % rate of smoking in adults in Europe [8]. In Spain, the 2006 National Health Survey (NHS) estimated a 29.5 % smoking rate in adults aged 16 and over [9], with approximately 53,155 smoking-attributable deaths in the same year [10]. Smoking prevalence among kidney transplant recipients is more difficult to estimate, and varies greatly across studies [11]. In a previous work, we found that up to 41.7 % of the renal transplanted patients in our center were smokers at the time of transplantation, and about 15 % continued smoking after the transplant [12]. Although this figure is not very high, the impact of smoking habit on the probability of cardiovascular events in the follow-up of kidney transplant recipients is clinically relevant. As stated in a previous paper, at the 5-year and 10-year follow-up, the number of patients needed to treat (NNT) who would have to give up smoking to prevent a cardiovascular event was 7 and 4, respectively [13].

A recent review [11] identified 12 studies in the period 1968–2009 reporting the effect of cigarette smoking on kidney allograft or recipient survival [14–25]. Although some of the revised studies showed contradictory results, in general cigarette smoking was associated with an increased risk of both graft loss and death. More recently, a large-scale study investigated the effect of smoking on post-kidney transplant outcomes in a retrospective cohort of 41,705 adult renal transplant recipients in the United States Renal Data System [26]. That work concluded that, compared with patients who have never smoked, new onset smoking after transplantation is associated with reduced allograft and patient survival. Similarly, a prospective study of 604 renal transplant recipients in The Netherlands showed that smoking after renal transplantation increases the risk of graft failure and mortality, while past smoking is a risk factor for mortality but not for graft failure [27]. Another European recent study in 402 randomly selected kidney graft recipients also concluded that smoking is a risk factor for kidney damage following renal transplantation [28].

Although there is evidence that active smoking plays an important role in allograft loss and patient mortality, this information has so far had little impact on patient management. Based on these results, smoking cessation should be promoted among patients undergoing kidney transplantation.

Both pharmacotherapy and non-pharmacological interventions could be used for the treatment of tobacco dependence. Non-pharmacological methods have the advantage of being inexpensive and feasible to implement, and may be particularly appropriate for transplant patients, who are usually polymedicated. The main non-pharmacological interventions for the treatment of tobacco dependence include advice from health professionals, self-help material, proactive telephone counseling, group or individual counseling, and intra-treatment or extra-treatment social support.

Although smoking cessation advice from a health professional improves smoking cessation rates, it is only moderately effective, with a smoking cessation rate only 1 to 3 % higher [29]. An alternative to increase smoking cessation rates could be to provide the patients with feedback on the physical effects of smoking via physiological measurements, such as measurement of carbon monoxide (CO) levels in exhaled air by CO-oximetry. Although a recent review could not demonstrate a significant benefit of interventions based on biomedical risk assessments, there is still insufficient evidence regarding this issue [30]. Furthermore, there is scarce data exploring the effect of these kinds of interventions on hospitalized patients or acutely ill patients. It is possible that such a specific context and the presence of co-existent illnesses could facilitate a modification of risk perception.

Currently, different projects are trying to determine the efficacy of adding spirometry or CO-oximetry information to brief advice on smoking cessation, in the primary health care setting [31, 32]. Measuring the level of CO in smokers’ exhaled air can motivate them to stop smoking or be a useful tool in monitoring their progress towards cessation. We aim to test its efficiency in a more restricted setting, studying its utility to promote smoking cessation among kidney transplanted patients. The objective of this study is to measure the effectiveness of exhaled CO plus brief advisory sessions, in comparison to brief advice, to reduce smoking exposure and smoking behavior in kidney transplant recipients who smoke. The effectiveness will be measured by:Self-reported tobacco use: abandonment of smoking habit and change in the number of cigarettes per day smokedAbandonment of smoking habit confirmed through a urinary cotinine testVariation in the motivational stages of change, according to the Prochaska and DiClemente’s Stages of Change model [33]Change in the motivation to giving up smoking, according to the Richmond test [34]Change in dependence, measured according to the Fagerström test [35]

## Methods/design

### Design and settings

This will be a single-centre prospective, randomized, controlled and open clinical trial with parallel groups set in the Nephrology Department at the Complexo Hospitalario Universitario A Coruña (northwest Spain). This is a 1382-bed public tertiary care hospital attending a population of nearly 560,000 habitants. The Nephrology department at Complexo Hospitalario Universitario de A Coruña is a reference hospital for renal transplantation at national level.

### Study period

Four years (from January 2012 to December 2015).

### Study population

All renal transplanted patients attending specialized consultations at the Nephrology department during the study period, who meet the inclusion criteria, are eligible to participate in the study. The flowchart of the study is shown in Fig. 1.

**Fig. 1 Fig1:**
[figure not shown]
Flowchart of the study

### Inclusion criteria

Adult (over 18 years of age) kidney transplant recipients who smoke, with functioning allograft, who underwent primary or repeated renal transplantation from a cadaveric or a living donor in the A Coruña Hospital between 1981 and 2014Current daily smokers. Smoking status is defined according to the WHO classification. Therefore, a patient is considered a current daily smoker if they report daily smoking during the previous month, irrespective of the number of cigarettes smokedPatients in the precontemplation, contemplation or preparation stages, based on Prochaska and DiClemente’s transtheoretical model [33]

Smokers in the precontemplation stage have not seriously considered giving up smoking and do not think they will do so within the next 6 months. For the individual the pros of continuing smoking clearly outweigh the cons. They can be in this condition because they are misinformed or poorly informed about the consequences of their conduct or because they have tried to change it several times and are demoralized because they were not able to do so. They tend to avoid reading, speaking or thinking about the risk. Smokers in the contemplation stage have seriously considered giving up smoking within the next 6 months. They have not considered giving up smoking within the next 30 days or have not tried to stop for at least 24 h in the last year. They worry about the risks, their motivation to change or to remain without changing, and also their intention of changing in the long term, within the next 6 months but without specifying when. The smokers in the stage of preparation for the action have considered giving up smoking within the next 30 days, besides having made an attempt to abandon the habit for a duration of at least 24 h in the last year. Otherwise, they will be said to be in the stage of contemplation.

### Exclusion criteria

Adult kidney transplant recipients whose grafts have failedNon-smoker and former smoker kidney transplant recipientsPatients in the action stage on Prochaska and DiClemente’s transtheoretical model [33]Patients with any chronic or terminal condition that complicates the study interventionsPatients with mental illness or transitory psychiatric deterioration at the moment of inclusion, who are not able to understand the study or complete the informed consent

### Recruitment of subjects

All renal transplanted patients will be contacted during their medical consultations at the hospital. They will be asked about their smoking habit. The patients who declare themselves smokers will be informed about the aims of the study and will be offered the chance to take part in it. An information sheet will be provided and informed consent will be obtained.

They will be asked about their consumption of tobacco and their attitude to giving up smoking with the aim of evaluating the phase of tobacco abandonment that they are on according to the process of change in Prochaska and DiClemente’s Stages of Change model [33].

Once the informed consent form has been signed each patient will be randomly assigned to the control group or the intervention group, according to the following scheme:Control group: brief advisory session to help give up smoking [36]Intervention group: brief advisory session on giving up smoking plus measurement of CO exhaled for CO-oximetry

### Sample size

Meta-analyses have shown that around 5–6 % of smokers stop after the brief advisory session from a physician [36]. A 13 % increase in the cessation rate for the brief advisory session plus CO-oximetry over the brief advisory session alone is considered clinically relevant. The sample target size is, therefore, 112 patients, with 56 patients in each group of the trial. Allowing for up to 10 % loss to follow-up, this would provide 80 % power to detect a 13 % difference in smoking cessation outcomes at a two-tailed significance level of 5 %.

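### The stated 80 % power for a 13-point difference in cessation does not follow from the plan's own inputs: 56 per group gives about 50–56 % after 10 % loss

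*Protocol article*

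**What the plan says.** The Sample size section of the protocol article gives every input of the calculation.

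- Control rate: "Meta-analyses have shown that around 5–6 % of smokers stop after the brief advisory session from a physician".
- Effect: "A 13 % increase in the cessation rate for the brief advisory session plus CO-oximetry over the brief advisory session alone" is called clinically relevant.
- Size: "The sample target size is, therefore, 112 patients, with 56 patients in each group of the trial".
- Loss: "Allowing for up to 10 % loss to follow-up".
- Claim: "80 % power to detect a 13 % difference in smoking cessation outcomes at a two-tailed significance level of 5" per cent.

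The abstract (Methods/design, Randomization) repeats the total, the group size, the loss, the power and the 13 %. It words the outcome differently: "difference in attempting to give up smoking outcomes at a two-tailed significance level of" 5 %.

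The Statistical analysis section compares proportions by chi-square or Fisher's exact test. The Outcome assessment section names the difference in mean urinary cotinine at 12 months as the main outcome.

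**The concern.** The Sample size section presents 112 as the consequence of its stated inputs, so the figure can be checked without any outside source. Rates near 5 % and 18 % with about 50 patients per group mean roughly 3 quitters against 9, which is too few for 80 % power.

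The 80 % is the design's justification. A reader, an ethics committee or a later reviewer would take it that the trial has four chances in five of detecting the effect it calls clinically relevant, when the chance is nearer one in two. The article says recruitment was under way at submission, so the statement could be corrected before results exist.

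The abstract adds a smaller inconsistency. An attempt to stop and cessation are different outcomes, and no control rate for attempts is given.

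**Working it through.** **Inputs.** All come from the Sample size section: control rate p1 = 0.05 to 0.06; difference d = 0.13, so p2 = 0.18 to 0.19; two-sided α = 0.05 (z = 1.960); power 0.80 (z = 0.842); loss 10 %; 56 randomised per group.

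**1. Trying to reproduce 56 per group.** The usual two-proportion formula, with pooled variance under the null and p̄ = (p1 + p2)/2, is

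n per group = [1.960·√(2p̄(1−p̄)) + 0.842·√(p1(1−p1) + p2(1−p2))]² / d²

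For 5 % v 18 %: p̄ = 0.115; first term 1.960 × 0.4512 = 0.884; second term 0.842 × 0.4417 = 0.372; sum 1.256; 1.256² / 0.0169 = 93.3.

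| Control v intervention | Evaluable per group | Per group after loss (÷ 0.9) | Total |
|---|---|---|---|
| 5 % v 18 % | 93.3 | 103.7 | 207 |
| 5.5 % v 18.5 % | 96.9 | 107.7 | 215 |
| 6 % v 19 % | 100.4 | 111.6 | 223 |

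Rounding up to whole patients before dividing by 0.9 gives 105, 108 and 113 per group. The plan's 56 per group is about half of what its inputs require.

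**2. Power of the planned size.** After 10 % loss, 56 × 0.9 = 50.4, so about 50 evaluable per group. The same formula solved for power is

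power = Φ{ [d·√n − 1.960·√(2p̄(1−p̄))] / √(p1(1−p1) + p2(1−p2)) }

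For 5 % v 18 % and n = 50: (0.13 × 7.071 − 0.884) / 0.4417 = 0.079, so power = 0.53.

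| Control v intervention | n = 50, formula | n = 50, exact chi-square | n = 56, formula | n = 56, exact chi-square |
|---|---|---|---|---|
| 5 % v 18 % | 53 % | 56 % | 58 % | 60 % |
| 5.5 % v 18.5 % | 52 % | 55 % | 56 % | 58 % |
| 6 % v 19 % | 50 % | 53 % | 55 % | 56 % |

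The exact columns enumerate both binomial distributions for the uncorrected chi-square test. With Fisher's exact test the power is 38–40 % at 50 per group and 44–47 % at 56.

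**3. Difference for which 80 % power exists.** By the same formula this is about 20–20.5 points with 50 per group and about 18–19 points with 56.

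**4. Other readings that might rescue the figure.**

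- Arcsine approximation: at most 57 % with 50 per group and 61 % with 56.
- One-sided test, contrary to the text: 63–66 % with 50 and 67–70 % with 56. The smallest requirement found (one-sided, arcsine, no loss, 5 % v 18 %) is 69 per group.
- Patients lost counted as smokers, all 56 per group analysed: rates shrink to 0.9 × 5 % = 4.5 % v 0.9 × 18 % = 16.2 % (or 5.4 % v 17.1 %), and exact chi-square power is 52–55 %.
- 13 % read as the intervention rate, 5–6 % v 13 %: 200–275 per group.
- 0 % v 13 %: 55.3, so 56 per group. This contradicts the stated 5–6 % and leaves no room for loss (55.3 / 0.9 = 61.4).

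**The case against.** The arithmetic itself has no good answer, but several things limit what may be built on it.

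- **Cause.** A reader might infer that 112 was the requirement for each group and was mistaken for the total. It fits at a 6 % control rate (111.6), but the same calculation gives 103.7 at 5 % and 107.7 at 5.5 %, and the section states a range. A calculation of 0 % v 13 % without loss also lands on 56 per group. The explanation is possible but the article does not show it, so it should not be recorded as fact.
- **Fisher's exact test.** One could headline power below 40 %. The analysis section offers chi-square or Fisher without assigning Fisher to this comparison. The chi-square figures are the fair ones to lead with; the Fisher figures show what happens if that test is used.
- **Main outcome.** One might read the result as about 50 % power for the trial's main analysis. The calculation concerns a cessation proportion, whereas the named main outcome is a mean cotinine difference, for which the Sample size section gives no mean or standard deviation. Nothing here says what the power for cotinine is, and that outcome does not make the cessation claim true.
- **Misreading a null result.** Nothing in the article says that a non-significant result would be taken as no effect. The absolute risk reduction with its 95 % confidence interval is already planned, so no extra rule on interpretation is needed.
- **Abstract.** The wording about attempts may be no more than loose phrasing for cessation. It is worth aligning but adds little weight.

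**Conclusion.** The power statement is wrong as written. For 5–6 % against 18–19 % cessation at two-sided 5 %, 56 randomised per group gives about 50–56 % power after 10 % loss and about 55–60 % with none (chi-square, approximate or exact), not 80 %. The stated inputs need about 93–101 evaluable per group, or about 104–112 randomised. The planned size has 80 % power only for a difference of about 18–20.5 points.

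This rests on reading 13 % as an absolute difference, which is how the section itself restates it, and on the stated 5–6 % control rate; every other assumption tried also falls short unless the control rate is set to zero. The conclusion covers cessation only. It does not extend to the mean cotinine outcome or to how the total was arrived at.

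**What to change.** In the Sample size section and in the abstract, replace the 80 % claim. State that 112 patients (56 per group, about 50 evaluable after 10 % loss) give about 50–56 % power for a 13-point difference from a 5–6 % control rate at two-sided 5 %, and 80 % power only for about 20 points. Say which test the figure refers to.

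In the abstract, name smoking cessation as the outcome, as the Sample size section does: "difference in smoking cessation outcomes at a two-tailed significance level of" 5 %.

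Add one sentence saying that this power concerns cessation and not the main outcome in the Outcome assessment section, the mean urinary cotinine difference at 12 months.

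The cost is wording and a less favourable power figure. Correcting the statement needs no extra patients. Keeping 80 % power for 13 points would instead need some 207–223 patients in total.

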### Blinding

This was an open clinical trial. Only those assessing outcomes were blinded after assignment to interventions.

### Random allocation to study arms

Computerized allocation to each of the study groups is done in advance. The assignment sequence is generated by a person who is not responsible for determining patient eligibility. By the nature of the interventions neither the researchers nor the patients can be blinded to the assignment.

### Intervention

At the baseline visit (visit 1) patients included in the study control group will be given a brief advisory session about giving up smoking. This will be firm, concise, personalized (trying to find the most important motivation for each patient) and appropriate to the phase towards cessation they are in. This will provide information about the negative effects of tobacco on their health and explain the main advantages of stopping smoking [36].

Patients included in the intervention group will receive the brief advisory session, as with the patients who belong to the control group, and in addition, CO-oximetry will be administered to them. This exploration allows one to know the amount of CO that the subject has in their body. The patient will take a deep breath and hold it for 15 s, then a slow, long and complete exhalation will be made. After a few seconds the oximeter indicator becomes stable and marks the exact number of particles per million (ppm) of CO that the subject has in the air they breathe. Follow-up visits will take place at 3 months (visit 2), 6 months (visit 3) and 9 months (visit 4). At each of these moments the anti-smoking advice will be repeated in the control group and anti-smoking advice plus CO-oximetry repeated in the intervention group (Table 2). At the 12-month (visit 5) visit, the anti-smoking advice will be given to both groups as well as CO-oximetry.

### Independent measures

From each patient included in the study the following variables will be recorded (Table 1):

**Table 1 Tab1:** Baseline and follow-up measurements

	Basal	3 months	6 months	9 months	12 months
Donor variables	x				
Age (years)					
Gender					
Type of donor (deceased versus living)					
Recipient variables	x				
Age (years)					
Gender					
Chronic kidney disease-related risk factors	x				
Primary kidney disease					
Renal replacement therapy before transplantation					
Duration of renal replacement therapy before transplantation					
Cold ischemia time					
Pre-transplant cardiovascular risk factors	x				
Weight (kg), height (m) and body mass index (kg/m^2^)					
Pre-transplant systolic and diastolic blood pressure (BP)					
Pre-transplant cholesterol (mg/dl), high-density lipoprotein (HDL) cholesterol (mg/dl), low-density lipoprotein (LDL) cholesterol (mg/dl), and triglycerides (mg/dl)					
Cardiovascular events before transplantation					
Previous malignancies					
Left ventricular hypertrophy					
Post-transplant cardiovascular risk factors		x	x	x	x
Body mass index (kg/m^2^)					
Post-transplant systolic and diastolic blood pressure (BP)					
New-onset diabetes mellitus after transplantation					
Post-transplant left ventricular hypertrophy					
Routine biochemistry at follow-up	x	x	x	x	x
Creatinine (mg/dl), proteinuria (g/day), leukocyte count (number/l), hematocrit (%), hemoglobin (g/dl), serum albumin (g/dl), total cholesterol (mg/dl), HDL cholesterol (mg/dl), LDL cholesterol (mg/dl), and triglycerides (mg/dl)					
Follow-up of kidney transplantation		x	x	x	x
Post-transplant cardiovascular events					
Acute rejection episodes					
Graft failure					
Infections					

Donor characteristics: age (years), gender and type of donor (deceased versus alive)Recipient features:Sociodemographic variables: age (years), genderChronic kidney disease-related risk factors: primary kidney disease, current treatment, previous transplants, cold ischemia timePre-transplant cardiovascular risk factors: weight (kg), height (m) and body mass index (kg/m^2^), basal cholesterol, systolic and diastolic pre-transplant blood pressure. Hypertension is defined as blood pressure above 140/90 mmHg. Pre-transplant hypercholesterolemia is considered as a cholesterol value above 200 mg/dl. Cardiovascular events before the transplant, tumors prior to transplant, smoking exposure prior to transplant, pre-transplant diabetes mellitus, and left ventricular hypertrophy will also be recordedPost-transplant cardiovascular risk factors: body mass index (kg/m^2^), systolic and diastolic blood pressure after transplantation, new appearance of diabetes mellitus after transplantation, left ventricular hypertrophy after transplantRoutine biochemistry on follow-up: creatinine (mg/dl), proteinuria (g/day), leukocyte count (number/l), hematocrit (%), hemoglobin (g/dl), serum albumen (g/dl), triglycerides (mg/dl), total cholesterol (mg/dl), HDL cholesterol (mg/dL), and LDL cholesterol (mg/dl)Transplantation outcomes in the follow-up: post-transplant cardiovascular events, acute rejection episodes, graft failure, and infectionsEvaluation of use of, and exposure, to tobacco:At the time of their incorporation in the study, the following information will be collected from all the patients:Self-reported smoking habit: number of cigarettes smoked per day and number of years of being smoker (the pack-years index will be computed)Number of previous attempts to stop smokingMaximum period of time elapsed without smokingConsumption of tobacco between their family and/or circle of friendsBoth at baseline and during follow-up at 3, 6, 9 and 12 months, the following information will be collected from each patient:Self-reported use of tobacco and number of cigarettes smoked per dayUrinary cotinine testStage of change, according to the Prochaska and DiClemente’s Stages of Change model (precontemplation, contemplation, preparation, abandonment) [33]Nicotine dependence measured by the Fagerström test [35]. This test is used to evaluate the degree of physical dependence on nicotine. It consists of six items with two or four possible answers. The score ranges from 0 to 10. The cutoff points are 4 and 7, where less than 4 means a low dependence, between 4 and 7 means a moderate dependence, and over 7 means high dependenceMotivation for giving up smoking, measured by the Richmond test [34]. This is a test that has four items with two or four possible answers. The score range is between 0 and 10, where item 1 rates between 0 and 1 and the other items range from 0 to 3.Based on this score, patients can be classified, according to their motivation for giving up smoking, in four groups: nil or low (0–3 points), doubtful (4–5 points), moderate (6–7 points), or high (8–10 points)

The results of the CO-oximetry in the intervention group will be collected at baseline, at 3 months, 6 months, 9 months and 12 months (visits 1–5). In the control group, CO-oximetry will only be performed at 12 months (visit 5).

